### Outcomes

The primary outcome is the proportion of procedures requiring perioperative allogenic RBC transfusion (within 7 days of surgery). Secondary outcomes are the quantity of blood transfused per procedure (RBC units), LoS per procedure (in days), critical care admission rate per 100 procedure (within 30 days post-surgery) and emergency readmission rate per 100 procedures (within 30 days post-surgery)
^1,
2,
17^.

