As individual-level data are available, including data on the treatment received as part of the anaemia screening programme, there are several ways the ‘anaemic’ subgroup can be defined and analysed to give different information. These will be explored as secondary analyses. The primary analysis will include all patients undergoing THR/TKR in the time period, with no splitting into anaemic or non-anaemic subgroups, to assess the impact of introducing the anaemia screening programme on the entire population of patients undergoing THR or TKR. Previous pre-post studies, on an earlier version of this dataset, suggest the effect size is large enough for this to show through even though only a subpopulation of patients receive treatment for anaemia. Secondary analyses such as splitting the data into those defined as being anaemic (by the anaemia pathway being used) or non-anaemic, allow for modelling with a control group and evaluation of the effects of the screening programme on the subpopulation expected to receive some treatment, (i.e. iron, GP or haematology referral), and hence benefit from introduction of the anaemia pathway. It may also be possible to explore, specifically, the effects of iron treatment on the subpopulation of anaemic patients eligible (ITT) or actually given (PP) iron as part of the anaemia screening programme.
Table 3 details the planned ITS analyses and, where appropriate, how the data will be split into two cohorts for secondary analyses. 

It is expected that the total number of procedures performed each month will be close to, or greater than, 100 for each time point in the primary analyses. However, as the data is split into cohorts (i.e. anaemic v non-anaemic), the number of procedures per month will reduce. This will likely increase the variability in the outcomes over time if reported as proportions (i.e. transfusion rate). Sensitivity analyses using event counts not rates will be conducted where the number of procedures per month drops below 30.

Time varying confounders specific to the primary outcome of this study may include other PBM interventions; those relevant will be discussed in turn. A restrictive blood transfusion policy was introduced Trust-wide in 2007 and has been unchanged since
^16,

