17^. A multimodal enhanced recovery programme (ERP), including IV TXA on induction of anaesthesia, was introduced in May 2008. In keeping with other similar policy changes in this unit, a 6-month implementation period for the ERP is considered appropriate. To account for this, data from 1
^st^ January 2008 to 31
^st^ October 2008 will be excluded from this analysis. In addition, patient warming has been introduced locally
^23^ but a Cochrane review shows this does not affect surgical transfusion rates, so will not be considered any further
^24^. Intra-operative cell salvage has never been routinely used locally for the procedures being studied. To the best of our knowledge, no other relevant co-interventions have been introduced during the study period. Any unaccounted for, gradual changes in practice, would be detected in the pre-intervention slope of the TXA analysis and in the control group for the anaemia analysis.

Other considerations include changes in data coding, validity and reliability over time. The data for this study is considered reliable as it comes from a number of NHS Trust electronic databases detailed earlier in this paper. There have been no material changes to data collection methods or outcome reporting over the study period.

Changes in the population over time can also affect ITS reliability. There have been no known substantial changes in the population served by NHCT over the study period; however, to explore this within the data, tables of patient demographics (i.e. age, sex) for each of the pre- and post-intervention periods will be produced and examined for differences. Should substantial differences be identified, these characteristics will be incorporated into the final model as covariates, where possible.

This study includes a continually enrolled population, so is not subject to population attrition over time. Although no changes to diagnostic criteria for ischaemic heart disease (IHD) are known to have occurred during the study period, this comorbidity is specifically mentioned in the NHCT transfusion policy and lowers the threshold for considering transfusion. For completeness, rates of IHD will be plotted against time and visually inspected for any patterns, particularly around the time of the interventions. If required IHD will be included in the ITS modelling.

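### Patient warming is ruled out as a confounder on transfusion evidence alone, which leaves length of stay, critical care admission and emergency readmission uncovered in the two uncontrolled interrupted time series

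*SAP article*

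**What the plan says.** The part of the Interrupted Time Series section on threats to validity introduces its list of co-interventions with a stated scope: "Time varying confounders specific to the primary outcome of this study may include other PBM interventions; those relevant will be discussed in turn". Within that list it records that "patient warming has been introduced locally" and closes the matter because "a Cochrane review shows this does not affect surgical transfusion rates, so will not be considered any further". No start date is given in the text, although a reference is cited for the local introduction. The article then says that, to the authors' knowledge, there were no other relevant co-interventions. It adds that gradual unlisted changes would show in the TXA pre-intervention slope or in the control group of the anaemia analysis.

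The Outcomes section goes beyond transfusion: "Secondary outcomes are the quantity of blood transfused per procedure (RBC units), LoS per procedure (in days), critical care admission rate per 100 procedure", and "emergency readmission rate per 100 procedures (within 30 days post-surgery".

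The ITS data description converts outcomes to monthly proportions or means for segmented regression. The TXA ITS has no control group. The primary anaemia ITS takes all patients without splitting them by anaemia status, so the non-anaemic control enters only in the secondary anaemia analyses of Table 3.

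**The concern.** The conclusion is wider than its premise. A finding of no effect on transfusion rates is a reason to ignore warming for transfusion. It is no reason to ignore it for length of stay, critical care admission or emergency readmission, and no other reason is offered. The statement on other co-interventions follows a review framed on the primary outcome, so it gives little assurance for these three.

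The safeguard named in the plan covers gradual change. A practice introduced at one time may act as an abrupt step, which a pre-intervention slope does not absorb. In a series without a control, such a step is divided between the trend, level-change and slope-change terms, and part or all of it can be read as the effect of the TXA policy or the screening programme. By contrast, the enhanced recovery programme is dated and handled by excluding January to October 2008. Warming receives neither a date nor any handling.

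**Working it through.** The plan states no figure on this point, so there is none to reproduce. The check asks how much of a warming step would be credited to each intervention.

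**Inputs (Table 3).** TXA: 33 pre months (November 2008 to July 2011), 6 excluded, 12 post. Primary anaemia ITS: 12 pre (February 2012 to January 2013), 6 excluded, 12 post (August 2013 to July 2014). Assumed, because the document does not give them: the warming start month, and its effect d on the outcome.

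**Method.** Intercept, trend, level change and slope change together amount to a separate straight line in each segment. A step inside one segment therefore disturbs only that segment's line. Take d = 1, a segment of n months, and a step at month m of it:

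- mean of the step: s = (n - m + 1)/n
- Sxx = n(n² - 1)/12, which is 143 for n = 12 and 2992 for n = 33
- fitted slope: b = (m - 1)(n - m + 1)/(2·Sxx)
- step in the pre segment: level-change bias = 1 - (s + a·b), slope-change bias = -b. Here a is the distance from the mid-point of the pre segment to the first post month: 19 - 6.5 = 12.5 for anaemia, 40 - 17 = 23 for TXA
- step in the post segment: level-change bias = s - 5.5b, slope-change bias = +b
- step in the lag, or at the first post month: pre line 0, post line 1, so level-change bias = 1 exactly

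| Layout and start | s | b | Level-change bias | Slope-change bias per month |
|---|---|---|---|---|
| Anaemia, pre-month 6 | 7/12 = 0.583 | 17.5/143 = 0.122 | -1.11d | -0.122d |
| Anaemia, pre-month 7 | 0.500 | 18/143 = 0.126 | -1.07d | -0.126d |
| Anaemia, pre-month 10 | 0.250 | 13.5/143 = 0.094 | -0.43d | -0.094d |
| Either, in the lag | - | - | +1.00d | 0 |
| Either, post-month 3 | 0.833 | 10/143 = 0.070 | +0.45d | +0.070d |
| TXA, pre-month 14 | 20/33 = 0.606 | 130/2992 = 0.043 | -0.61d | -0.043d |
| TXA, pre-month 33 | 1/33 = 0.030 | 16/2992 = 0.005 | +0.85d | -0.005d |

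Over all start months, the level-change bias runs from -1.11d to +1.00d (anaemia) and from -0.61d to +1.00d (TXA). A start outside a window gives zero bias in that analysis. The twelve months from February 2012 to January 2013 serve both analyses, so a start after the first of them would disturb both.

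**Precision cost of a step term.** With c the level-change bias multiple, R = S - S²/n - b²·Sxx (S the number of months in the segment at or after the step), and V = 1/n + a²/Sxx + 1/12 + 5.5²/143 (n, a and Sxx of the pre segment), the level-change standard error is multiplied by √(1 + c²/(R·V)).

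- Anaemia, pre-month 6: V = 1.471, R = 7 - 4.083 - 2.142 = 0.775, c² = 1.239, factor √2.087 = 1.44.
- TXA, pre-month 33: V = 0.502, R = 1 - 0.030 - 0.086 = 0.884, c² = 0.717, factor √2.615 = 1.62.
- Lag: R = 0 within the fitted months once the level change is in the model, so the term cannot be estimated.

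These are ordinary least squares figures. The planned autocorrelation adjustment would change the weights and hence the partial multiples, but not the complete aliasing in the lag.

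**The case against.** Four points can be made for the plan.

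- **No bias is demonstrated.** Every figure above is a multiple of an unknown d at an unknown date, and nothing in the article shows that warming affects the three outcomes. The source cited for the local introduction may give the date, and a condensed article need not repeat it. This stands: the finding concerns the stated reasoning, not a demonstrated error in a result.
- **The scope is declared.** The list is introduced as specific to the primary outcome, and Table 3 does not assign outcomes to analyses. On a narrow reading, warming is dismissed for transfusion only. But the dismissal itself carries no such limit, and no second review for the other outcomes follows. That these outcomes enter the ITS is an inference from the Outcomes section and the data description, though a natural one.
- **The screening question has other protection.** The three secondary anaemia ITS use a non-anaemic control, where a step common to both groups cancels. The regression discontinuity design covers the primary and secondary outcomes and compares patients across a haemoglobin threshold, where a calendar-time step creates no jump. This stands and narrows the exposure. Neither check exists for the TXA policy.
- **The plan concedes unmeasured confounding.** It does so when comparing the two designs. Warming, however, is known and named.

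A reader might infer that the transfusion result is compromised, that all the screening evidence is exposed, or that warming has in fact distorted these outcomes. The document supports none of these: the ground given does cover transfusion, the controlled ITS and the discontinuity design are largely protected, and neither date nor effect is known.

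**Conclusion.** The concern holds in a limited form. The plan's reason for setting warming aside does not extend to length of stay, critical care admission or emergency readmission. The exposure lies in two places: the TXA ITS, which serves the secondary aim, and the uncontrolled all-patient anaemia ITS. Depending on the start month, a warming step could add to, mask or reverse an intervention effect on these outcomes, within the multiples of d given above.

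This rests on three assumptions: that the three outcomes are analysed by ITS, that warming began inside a window, and that it acts on them as a step. If either of the last two fails, this step bias is absent. Protection in the controlled ITS is full only if warming acts equally in anaemic and non-anaemic patients.

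**What to change.** Analysis is still pending according to the Study status section, so this can be pre-specified.

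1. Confine the dismissal of warming, and the statement that there were no other relevant co-interventions, to the transfusion outcomes.
2. State the month warming was introduced and compare it with the TXA window (November 2008 to January 2013) and the anaemia window (February 2012 to July 2014). For the planned sensitivity analysis, compare it also with the extended post-intervention period to February 2019.
3. If it falls inside a window, add a sensitivity model with a warming step term for the three non-transfusion outcomes.
4. If it falls in a lag period, report that the effects cannot be separated with those months excluded. Rely on the controlled ITS and the regression discontinuity design for the screening question. For TXA no such fallback exists, so report it as a limitation.

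The cost is one date from the department and one extra model for three secondary outcomes. That model has wider intervals: the level-change standard error rises by up to about 44% in the 12/6/12 layout, and by up to about 60% in 33/6/12 when the step lies next to the lag. This is why it belongs in a sensitivity analysis and not in the main model.

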### Interrupted Time Series

ITS using segmented regression has several strengths over the pre-post study design. It controls for secular trends over time, provides powerful, easy to understand visual outputs, and may improve generalisability to the wider population
^7,
8,
19^. For this study, data are available to evaluate both policies described above in an ITS analysis.

The two interventions in this study were introduced at specific, well defined time points, allowing for clear separation of pre- and post-intervention periods.
Figure 1 provides a timeline for the interventions in questions and
Table 3 provides details of the planned analyses and time periods included in each. As shown in
Figure 1, the same 12-month time period is used for both ITS analyses meaning they are not independent. However, there is insufficient time or data points to prevent this overlap, and this will be discussed as a potential limitation of the study.

**Table 3. T3:** Planned ITS analyses.

Policy change	Dates	Analyses
Change in TXA dose policy	Pre-intervention 01/11/2008 – 31/07/2011 Excluded implementation (lag) period 01/08/2011 – 31/01/2012 Post-intervention * 01/02/2012 – 31/01/2013	PRIMARY – Population-level effects of TXA policy for all patients undergoing THR or TKR
Introduction of preoperative anaemia screening programme	Pre-intervention * 01/02/2012 – 31/01/2013 Excluded implementation (lag) period 01/02/2013 – 31/07/2013 Post-intervention 01/08/2013 – 31/07/2014 (sensitivity analysis 01/08/2013 – 28/02/2019)	PRIMARY – Population-level effects of anaemia screening programme for ***all patients*** undergoing THR or TKR (with equal number of data points pre- and post-intervention)
		SECONDARY - Effect on anaemic subpopulation ***eligible for any*** ***treatment*** as per anaemia pathway (Hb <120g/L, female or 130g/L, male) **, modelled against non-anaemic cohort
		SECONDARY - Effect on anaemic subpopulation ***eligible for iron*** treatment only (Hb 105–119g/L female, 115–129g/L male & ferritin 12- 100), modelled against non-anaemic cohort (excluding those with Hb <105 or <115 and those referred to GP/haematologist).
		SECONDARY - Effect on anaemic subpopulation ***given iron*** treatment only (as above but only those given iron), modelled against non-anaemic cohort (same exclusion as above) – per protocol analysis

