21^. In keeping with many ITS studies, individual-level outcome data will be converted to, and presented as, proportions or means at monthly intervals and a segmented-regression analysis performed
^21^. ITS plots will be generated and visually inspected to determine if linear or non-linear regression modelling is appropriate. A minimum of 8 data points pre- and post-intervention are desirable
^20,
21^. It is expected the shortest time frame being analysed in this study will include 12 months/data points, thus surpassing this requirement. The power of an ITS analysis is increased if there are an equal number of data points pre- and post-intervention
^22^. In the case of preoperative anaemia screening there are expected to be 12 data points in the pre-intervention period but 60 in the post-intervention period. As such, to increase power of this analysis this period will be cut to include only 12 time points, after the 6 month lag period, for the primary analysis of the anaemia screening policy. Sensitivity analysis including all post-implementation data points will be conducted.

***Addressing threats to validity.*** Time varying confounders are the main threat to the validity of ITS studies
^21^. These are specific to each ITS study and are carefully considered later in this SAP. However, the most robust way to account for time varying confounders, even those that are unknown, is to model against a control group. This could either be a different population not exposed to the intervention or, if individual-level data are available, by splitting the data into two groups, one group targeted by an intervention and another that is not. In this study, data for a different group of patients is not available for either intervention. The TXA policy is targeted at all THR or TKR patients so this data cannot be split. However, the anaemia screening policy targets a specific subgroup of anaemic patients with treatments so the population can be split into two groups to increase the robustness of this analysis. As such the two interventions will be modelled separately: 1) the TXA intervention without a control group, and 2) the anaemia screening intervention with a control group.

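### The TXA pre-intervention slope ends in July 2011, so it cannot detect any gradual change in practice that starts later, as the plan says it would

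*SAP article*

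**What the plan says.** The TXA row of Table 3 sets three windows:

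- baseline: "Pre-intervention 01/11/2008 – 31/07/2011"
- gap: "Excluded implementation (lag) period 01/08/2011 – 31/01/2012"
- effect window: "Post-intervention * 01/02/2012 – 31/01/2013"

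Outcomes are to be analysed as "proportions or means at monthly intervals and a segmented-regression analysis performed". The shape of the trend is left open: "ITS plots will be generated and visually inspected to determine if linear or non-linear regression modelling is appropriate". No model equation is written out.

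Under Addressing threats to validity (Interrupted Time Series), the article names time-varying confounding as the chief threat to this design and a control series as the strongest defence, including against unknown confounders. It then says the two policies will be modelled as "1) the TXA intervention without a control group, and 2) the anaemia screening intervention with a control group". After reviewing known co-interventions it adds: "Any unaccounted for, gradual changes in practice, would be detected in the pre-intervention slope of the TXA analysis". The rest of that sentence relies on the control group for the anaemia analysis. That part is a separate matter and was not tested here.

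**The concern.** A slope fitted to months up to July 2011 carries information only about those months. It can account for a trend already running through the baseline and continuing in the same shape. A change in practice that begins in the six excluded months or in the effect window leaves no trace in it. One that begins late in the baseline is diluted by the earlier flat months. The word *any* therefore claims a protection that the TXA design does not have.

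At stake is the primary analysis of the secondary aim. A background fall in transfusion beginning after July 2011 would appear as a level and slope change credited to the higher-dose policy, and the stated safeguard would not flag it. The other planned checks do not fill the gap. The demographic tables and the plot of ischaemic heart disease concern patient mix rather than practice, and the sensitivity analyses concern outliers, autocorrelation, seasonality and subgroups.

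**Working it through.** The plan gives no bias or power figure on this point, so there is none to reproduce.

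**Inputs from Table 3.** Baseline: months 1 to 33. Excluded: months 34 to 39. Effect window: months 40 to 51, midpoint 45.5.

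**Model (assumed).** This is the usual reading of segmented regression: outcome = a + b·t + c·post + d·post·(t − 40), fitted by least squares. Because the post period has its own level and slope, the fitted baseline line depends on months 1 to 33 only. The lagged residual terms were not modelled.

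**Test signal.** True TXA effect zero; background drift of 1 unit a month after month s, that is max(0, t − s). The spurious TXA effect at mid-window is the mean drift over months 40 to 51 minus the baseline line extended to month 45.5.

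**Drift from the end of July 2011 (s = 33).** Every baseline value is 0, so the fitted slope is 0. Mean drift in the window is 45.5 − 33 = 12.5, and all 12.5 counts as TXA effect (100%). For a fall of 0.1 percentage points a month, the false effect is −0.7 points in February 2012, −1.25 at mid-window and −1.8 in January 2013.

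**Drift from 6 months before the policy (s = 27).**
- Baseline sum of squares of time: 33 × (33² − 1)/12 = 2992.
- Cross-product: 11·1 + 12·2 + 13·3 + 14·4 + 15·5 + 16·6 = 301, so the slope is 301/2992 = 0.101.
- Baseline mean: 21/33 = 0.636. Line at 45.5: 0.636 + 0.1006 × 28.5 = 3.50.
- Actual mean drift: 18.5. Spurious effect: 15.0, or 15.0/18.5 = 81%.

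**Other starts, same method.**

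| Drift starts | Fitted baseline slope (true 1) | Share counted as TXA effect |
|---|---|---|
| Throughout baseline | 1.00 | 0% |
| 18 months before policy | 0.59 | 28% |
| 12 months before | 0.32 | 53% |
| 6 months before | 0.10 | 81% |
| 3 months before | 0.03 | 93% |
| End of July 2011 or later | 0.00 | 100% |

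**If another form is chosen.** With a quadratic baseline, a drift starting after July 2011 still counts at 100%. The share falls to 74% for a start 3 months before and 36% for 6 months before; at 12 months before, the curve over-corrects (−22%). A level-change-only model still assigns 80 to 90% of a drift starting between the end of July 2011 and the start of February 2012.

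**Illustrative false-positive rates.** Assumptions not in the plan: 8% transfused, 80 procedures a month, independent months, and a drift of 0.1 or 0.2 points a month from August 2011. Monthly SD = 100 × √(0.08 × 0.92/80) = 3.03 points. Each standard error is a design factor times 3.03, and the test is two-sided at 5%.

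| Contrast | Factor | SE (points) | Bias at 0.1 / 0.2 | False positives at 0.1 / 0.2 |
|---|---|---|---|---|
| Level change | 0.709 | 2.15 | 0.7 / 1.4 | 6% / 10% |
| Slope change (per month) | 0.0856 | 0.26 | 0.1 / 0.2 | 7% / 12% |
| Mid-window effect | 0.621 | 1.88 | 1.25 / 2.5 | 10% / 26% |

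The article expects monthly volume close to or above 100. At 100 a month the rates are about 7% / 11%, 7% / 14% and 12% / 32%.

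**The case against.** The strongest reply is that this limit belongs to every uncontrolled interrupted time series and is largely disclosed. The article says that TXA has no control group and that none is available. Under Comparing ITS and RDD it lists unmeasured confounders as a limitation and says the design supports association rather than causation. Nothing in the document points to an actual change in practice after July 2011.

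Much of that stands. A reader might infer that the authors will present the TXA result as secured against background drift, or that this sentence ends their treatment of confounding. The document supports neither reading: the general caveats are there, and the section goes on to data coding, population change and heart disease. A reader might also take 10% or 26% as the error rate of the planned test. Those rates belong to a mid-window contrast the plan never names, under assumed inputs; for the usual level and slope coefficients they are much smaller. The late-baseline shares likewise depend on a linear form the plan does not fix.

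The sentence itself is not rescued. General caveats do not correct a specific assurance, and the passage on unmeasured confounders says the design has tried to address them. Condensing a plan into an article does not explain a statement that the article's own dates contradict.

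**Conclusion.** The statement is incorrect for the TXA analysis. From the plan's dates alone, a slope ending on 31 July 2011 cannot detect a change that starts afterwards. Under a linear level-plus-slope model, such a drift enters the mean TXA effect in full, and this also holds with a quadratic baseline. For drifts starting 12 or 6 months before the policy the share is about 53% or 81%, conditional on a linear baseline. Only a linear trend across the whole baseline is fully removed.

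This is a false assurance about what the TXA analysis can exclude. It is not evidence that a drift occurred or that the estimate is biased. It concerns the secondary aim and changes no model or dataset. The false-positive rates show direction and rough size only. The correction should be made before analysis, which the article says is still pending.

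**What to change.** Replace the TXA part of the sentence with: *The pre-intervention slope accounts only for changes already under way and approximately linear during November 2008 to July 2011; changes in practice starting later cannot be separated from the TXA policy.* Carry the same limit into the TXA conclusion.

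As a labelled sensitivity illustration, report the constant background slope change from August 2011 that would bring the mid-window TXA effect to zero (estimate divided by 12.5 months), and the one that would bring its confidence limit to zero (that limit divided by 12.5). Show both beside the baseline slope and its 95% interval. This figure assumes a linear drift starting in August 2011 and should not serve as a decision rule.

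The cost is one reworded sentence and two divisions per TXA outcome from the model already fitted, with no new data. The downside is that the stated protection of the TXA result becomes less favourable.
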